## *6.2 Assessment of the primary endpoint (efficacy)*

The primary endpoint will be the mean change in gait speed at discharge. Particularly, expecting a treatment effect also on the duration of hospital stay, the change over time will be normalized by the duration of observation in months. Gait speed will be evaluated by the 4-meter walking test, asking the patients to walk at their usual pace. Patients will be allowed to use an assistive device, if needed. Specifically, the patient will be asked to walk down a hallway through a 1-metre zone for acceleration, a central 4- metre “testing” zone, and a 1-metre zone for deceleration (the patient should not start to slow down before the 4-metre mark), starting and stopping the timer with the first footfall after the 0-metre line and the 4-metre line, respectively. The best time of two attempts will be taken into account.

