***2.1 Primary endpoint***

The primary endpoint will be the mean change in gait speed per month (m/s/month) during the 4-meter walking test.

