***2.2 Secondary endpoints***

The following key secondary endpoints (change per month in physical performance outcome measures) will be investigated:

- chair-stand test
- Timed up and go (TUG) test
- Short Physical Performance Battery (SPPB)

The following secondary endpoints will be also addressed:

- change per month in handgrip strength
- change per month in Tinetti scale
- change per month in Barthel Index
- change per month in activities of daily living (ADL) score
- change per month in body weight
- change per month in appendicular muscle mass (AMM)
- change per month in skeletal muscle mass index (SMMI)
- change per month in cognitive status (Trail making test and Mini Mental State Examination [MMSE])
- change per month in quality of life (Short-Form 12-Item Health Survey [SF-12])
- the proportion of patients who improved their rehabilitation intensity profile
- the modality of discharge (home vs. institution)
- the overall economic benefits (using length of stay [LOS] and total duration of rehabilitation [minutes] as surrogate measures)
- safety of the intervention

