# **Intervention**

## *5.1 Physical intervention*

An individualized, moderate-level (Borg Rate of Perceived Exertion scale score of 12-14) physical fitness and muscle mass promoting program will be set up for all in-patients. Trained staff will supervise all exercise sessions, monitoring the individual exercise ability of each patient and adjusting the intensity level, as appropriate. The intervention will consist of exercise sessions daily, 5 times/week. The initial duration of each session will be 20 minutes and it could be increased progressively, along with the intensity of the exercises, up to 30 minutes. All sessions will include the following:

- 5-minute warm-up

- 5-to-10-minute progressive sequence from seated to standing muscle-strengthening exercises: toe raises, heel raises, knee lifts, knee extensions in the seated position; hip flexions and lateral leg raises standing next to a chair used for stability; ankle-weight bearing exercises (seated knee flexion and extension, standing knee flexion and extension), with weights ranging from 0.5 to 1.5 kg as appropriate (in accordance with each participant’s strength as the resistance progressively increased); leg extensions and hip flexions using resistance bands. Upper-body exercises will be also performed and included double-arm pull downs and biceps curls. Patients will be asked to perform up to 8 repetitions, as appropriate

- 5-to-10-minute balance and gait exercises: one-leg stands, tandem stands, multidirectional weight shifts, tandem walk, as well as practicing proper gait mechanics focusing on balance maintenance and increasing stride length, while changing direction and/or gait pattern

- 5-minute cool-down.

The minimum duration of the physical intervention program will be 4 weeks and it could be prolonged up to 8 weeks according to the results obtained. Specifically, the decision to finish the rehabilitation and to discharge the patient will be taken by a multidisciplinary team (geriatrician, physiatrist, physiotherapist and nurse) once the duration of each exercise session is stabilized to 30 minutes and no increase in intensity could be considered for 5 consecutive days.

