***8.2 Statistical analysis***

The efficacy analysis population will include the patients reaching the primary endpoint evaluation and it will be performed according to the intention to treat principle.

All patients consuming at least one serving of nutritional formula will be included in the safety analysis.

Descriptive statistics: Mean and standard deviation, range, median and quartiles will be calculated for continuous variables. Frequencies and percentages will be calculated for categorical variables.

Analysis of study endpoints: Expecting a treatment effect also on the LOS, changes over time in both primary and secondary continuous outcome variables will be normalized by the duration of observation in months. Changes will be calculated so that an improvement would result in a positive value in favor of the experimental formula (as either final - initial value or initial - final values).

*Primary endpoint* - The change in gait speed will be compared between groups with a generalized linear regression model using Huber-White robust standard errors to account for variance inhomogeneity. Then a series of supportive analyses of the primary endpoint will be performed. First, we will conduct a multivariable model, to adjust for potential confounders regardless of differences in baseline features, including gender, age and monthly change in energy intake, creatinine and in total cholesterol. Second, a conservative sensitivity analysis of the primary endpoint using the worst possible outcome of the study for patients dropping out will be performed.

*Secondary endpoints* - Group comparison will be performed for all secondary endpoints on a continuous scale using an unadjusted generalized linear regression model. For both primary and secondary outcome variables the mean change within groups will be also assessed. For secondary endpoints on a binomial scale, a generalized linear model for the binomial family will be used. For all endpoints the treatment effect (mean or frequency difference) and 95% confidence interval (CI) will be reported.

All statistical analyses will be performed using the software STATA 15.0 statistical software (Stata Corporation, College Station, TX).

Dropout

The following causes of dropout will be considered:

- Death

- Lost to follow-up (due to hospitalization or transfer to another setting of care)

- Withdrawal

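### Gait-speed change per month mixes gain with length of stay, and no planned analysis shows the gain itself

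*Protocol*

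**What the plan says.** Protocol section 2.1 defines the outcome as a rate: "The primary endpoint will be the mean change in gait speed per month (m/s/month) during the 4-meter walking test". Section 6.2 opens with "The primary endpoint will be the mean change in gait speed at discharge" and then divides that change by time, because it anticipates "a treatment effect also on the duration of hospital stay, the change over time will be normalized by the duration of observation in months". Section 8.2 extends the rule: "changes over time in both primary and secondary continuous outcome variables will be normalized by the duration of observation in months". Section 2.3 also lists protein and energy intake among exploratory changes per month.

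The time divided by is not fixed. Under section 5.1 the programme lasts at least 4 weeks and can run to 8, depending on results. A multidisciplinary team ends it "once the duration of each exercise session is stabilized to 30 minutes and no increase in intensity could be considered for 5 consecutive days". The schedule in the Methods section has physical performance measured only at baseline and at the end of study.

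Section 8.2 names two supportive analyses of the primary endpoint. One is a model adjusted for sex, age and the monthly changes in energy intake, creatinine and cholesterol. The other is a worst-outcome analysis for drop-outs. Neither examines the change in gait speed before division. Length of stay is a separate secondary endpoint (section 2.2), used as a surrogate for economic benefit.

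**The concern.** Dividing by time is harmless for interpretation when time is unrelated to treatment. Here the protocol divides precisely because it expects treatment to change the time. The ratio then carries two possible effects, on how much patients gain and on how long they stay, and one p-value cannot separate them.

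The stated objective is efficacy on physical performance and on functional and muscle mass recovery. If the formula only brings discharge forward, the primary result can favour it although patients leave walking no faster than controls. If the formula lets patients go on progressing, the discharge rule can prolong their stay, and the ratio can understate a larger gain. With only two assessments, no measurement at a common time is available to settle which has happened.

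The same division is also applied to protein and energy intake. Supplementation makes these step up at the start rather than accumulate, so a per-month value has no clear meaning.

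**Working it through.** **1. The plan's own figure.** Section 8.1 gives effect size 0.5, two-sided 5% and 80% power. A two-sample t-test needs 63.8, so 64 per arm and 128 in total, with power 0.801. The figure is reproduced. It is standardised, so it supplies no gain, SD or stay difference; those used in steps 3 to 5 are assumptions.

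**2. Arithmetic of the ratio.** Months = weeks × 7 / 30.4375, so 4, 5, 6 and 8 weeks are 0.920, 1.150, 1.380 and 1.840 months. The allowed stay varies by a factor of 2. The gains below are illustrative.
- Same gain, different stay: 0.20/1.380 = 0.145 and 0.20/1.840 = 0.109 m/s/month. The shorter stay scores 33% higher.
- Larger gain, lower score: 0.30/1.840 = 0.163, against 0.20/1.150 = 0.174.

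**3. If total gain does not depend on stay.** Assumed: control gain 0.20 m/s, SD 0.15, 63 per arm (70 × 0.9), stay SD 1 week limited to 4–8 weeks, Welch test, 20,000 simulated trials per row. Entries are the chance of a significant result favouring the experimental formula.

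| Gain, exp. vs control (m/s) | Nominal mean stay, exp. vs control (weeks) | Per month | Un-normalised |
|---|---|---|---|
| 0.20 vs 0.20 | 6 vs 6 | 2.6% | 2.7% |
| 0.20 vs 0.20 | 5.75 vs 6.25 | 8% | 2.5% |
| 0.20 vs 0.20 | 5.5 vs 6.5 | 21% | 2.6% |
| 0.20 vs 0.20 | 5 vs 7 | 61% | 2.4% |
| 0.25 vs 0.20 | 7 vs 5.5 | 2% | 46% |

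**4. If gain accumulates in proportion to time.** Assumed: control rate 0.145 m/s/month, SD 0.109 (the values in step 3 divided by 1.380 months), other settings unchanged.

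| Rate, exp. vs control (m/s/month) | Nominal mean stay, exp. vs control (weeks) | Per month | Un-normalised |
|---|---|---|---|
| 0.145 vs 0.145 | 6.5 vs 5.5 | 2.5% | 21% |
| 0.145 vs 0.145 | 7 vs 5 | 2.4% | 59% |
| 0.20 vs 0.145 | 5.5 vs 6.5 | 80% | 27% |
| 0.20 vs 0.145 | 5 vs 7 | 80% | 3% |

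The picture is reversed: the un-normalised change now reflects stay.

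**5. Sensitivity of step 3.** With control gain 0.10 m/s, SD 0.05 to 0.15 and 64 per arm, equal gain and an experimental stay shorter by a nominal 1 or 2 weeks give a favourable per-month result in 9% to 92% of trials. With a true 0.5 SD larger gain and a stay longer by 1 or 2 weeks, power of the per-month test is 0.1% to 49%, against 80–81% for the un-normalised change. The direction is stable; the size is not.

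**6. Step-type variables.** Two servings of 20 g (section 5.2) add 40 g protein a day from the start if fully consumed, and section 6.1 counts the supplement in recorded intake. Then 40/0.920 = 43 and 40/1.840 = 22 g/day/month, from stay alone. For energy, 2 × 150 = 300 kcal a day becomes 326 or 163 kcal/day/month. Monthly energy change is a covariate in the first supportive model, so that covariate partly encodes stay.

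**The case against.** The strongest reply is that gain per month is a deliberate and openly stated estimand. Sections 2.1, 6.2 and 8.2 agree on it and give the reason. Under it, reaching the same gain sooner is a benefit. This stands. A reader might infer from step 3 that the primary test has an inflated false-positive rate. The documents do not support that: the test holds its level when treatment changes neither gain nor stay, and in the 21% and 61% rows the rate per month really is higher.

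The second reply is that un-normalised change at discharge is also measured at a response-dependent time. This stands too, as step 4 shows. It rules out treating the raw change as the correct analysis, or requiring it to be favourable before the primary claim is accepted. If both arms leave at a similar plateau, such a requirement could suppress a real effect on speed of recovery.

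Third, a reader might infer that the ratio will hide a true gain. That needs a longer experimental stay, and the protocol does not say which way it expects stay to move.

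Fourth, length of stay is already an endpoint with an estimate and 95% CI, which is a safeguard rather than double counting. An analysis plan not shown here could also add the raw change, and the data for it are collected. But section 8.2 itself names the supportive analyses, and nothing there ties the stay result to the reading of the primary.

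**Conclusion.** The point holds as one of interpretation, not of test validity. The primary outcome divides by a post-randomisation, response-dependent stay that the protocol expects treatment to alter. A significant difference in m/s/month cannot by itself be read as greater gait speed at discharge. The twofold range of the divisor and the reversal in step 2 are arithmetic. The percentages in steps 3 to 5 rest on assumed gains, SDs and stay differences, and on whether gain depends on time in hospital, which the documents do not settle. A half-week difference in mean stay moves the 2.5% only to about 8% under step 3. The intake point is minor but clear: a per-month value for a step change depends on stay alone.

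**What to change.** Keep the monthly rate as primary. In section 8.2:
- Add, as a named supportive analysis, the un-normalised change in gait speed from baseline to discharge, adjusted for baseline. Do the same for the chair-stand test, TUG and SPPB.
- Report each beside its monthly rate and the between-arm difference in length of stay.
- State how conclusions will be worded: a rate difference without a difference in gain is described as faster recovery or shorter stay, not as greater gait speed at discharge. Do not make the un-normalised result a condition for the primary claim.
- Analyse protein and energy intake as plain change, including where energy intake is a covariate in the adjusted model, and amend section 2.3 to match.

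The cost is some wording and one extra model per endpoint on data already collected. The downside is a narrower claim if the result is driven only by stay. Specifying this before unblinding keeps the reading from being post hoc.

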## *6.3 Assessment of safety*

Based on previous trials investigating the use of this food for special medical purposes, the proposed intervention is considered to be safe. Patients will be actively monitored for the occurrence of any potential gastrointestinal side effect associated with the consumption of the nutritional intervention formula (common adverse events). The occurrence of any unexpected serious adverse event will also be recorded.

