***2.3 Other pre-specified study endpoints***

As explorative endpoints, we will also consider changes (per month) in: protein and energy intake, Mini Nutritional Assessment (MNA®) score, C-reactive protein, vitamin D, total cholesterol, albumin and creatinine.

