## *4.2 Exclusion criteria*

- Any malignant disease during the last five years
- Known kidney failure (previous glomerular filtration rate <30 ml/min);
- Known liver failure (Child-Pugh class B or C)
- Known psychiatric disorder
- Endocrine disorders associated with disorders of calcium metabolism (except osteoporosis)
- Indications related to the study product:
  - - More than 10 µg (400 IU) of daily Vitamin D intake from medical sources
    - More than 500 mg of daily calcium intake from medical sources.
    - Adherence to a high energy or high protein diet up or use of protein containing or amino acid containing nutritional supplements up to three months before starting the study.
- Known allergy to milk, milk products or other components of the proposed interventions
- Indication to or ongoing artificial nutrition support
- Inclusion in other nutrition intervention trials
- Investigator's uncertainty about the willingness or ability of the subject to comply with the protocol requirements
- Refusal

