*Quality of life assessment*: participants will be tested with the Short-Form 12-Item Health Survey (SF-12), a short, generic health‐status measure reproducing the 2 summary scores of the SF‐36 - the physical component summary (PCS) score and the mental component summary (MCS) score – by addressing 8 health domains (physical functioning, role physical, bodily pain, general health, vitality, social functioning, role emotional, and mental health.

*Biochemical assessment*: venous blood samples will be drawn after an over-night fast and used for the evaluation of routine parameters (total blood count, glucose, transaminases, albumin, creatinine, blood urea nitrogen, serum electrolytes, transferrin, total cholesterol), as well as C-reactive protein and 25-hydroxyvitamin D (25(OH)D) levels.

*Assessment of complexity of assistance needs*: the rehabilitation profile system will be used to rate the complexity of assistance needed by the patient. Profiles are defined according to the assessment of 4 kinds of intervention and their interaction (general assistance, functional reactivation and recovery, medical support and social support). Patients entering an intermediate rehabilitation program as in-patients can be assigned any one of 5 different profiles:

- Profile 1: low assistance and medical needs; patient requires mainly general assistance;
- Profile 2: intermediate general assistance needs, but low medical needs; patient requires mainly general assistance, as well as functional reactivation and recovery;
- Profile 3: high general assistance needs and intermediate medical needs; patient requires mainly general assistance, functional reactivation and recovery, as well as intermediate medical support;
- Profile 4: high assistance and medical needs; patient requires general assistance, functional reactivation and recovery, as well as medical support on account of important concomitant diseases;
- Profile 4B DEMENTIA: high assistance and medical needs. Patient suffers from dementia and therefore requires a lot of general assistance, functional reactivation and recovery, as well as medical and social support provided by highly trained professionals.

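### Renal, electrolyte and vitamin D blood values are taken at both visits, but section 6.3 makes none of them a safety outcome

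*Protocol*

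**What the plan says.** Protocol section 6.3 is the whole of the safety assessment. It has two parts:

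- Active monitoring: "Patients will be actively monitored for the occurrence of any potential gastrointestinal side effect associated with the consumption of the nutritional intervention formula".
- Serious events: "The occurrence of any unexpected serious adverse event will also be recorded".

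Elsewhere, safety is listed once among the secondary endpoints (section 2.2), has one row in the schedule of assessments marked at end of study only, and has an analysis population in section 8.2 (everyone who took at least one serving). None of these says what the safety data contain.

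Section 4.2 excludes patients with "Known kidney failure (previous glomerular filtration rate <30 ml/min") and those with endocrine disorders that disturb calcium metabolism. In a separate sub-list tied to the study product it also excludes patients with "More than 10 µg (400 IU) of daily Vitamin D intake from medical sources" or "More than 500 mg of daily calcium intake from medical sources".

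The biochemistry panel in section 6.1 includes "glucose, transaminases, albumin, creatinine, blood urea nitrogen, serum electrolytes", together with 25(OH)D. The schedule marks biochemistry at baseline and at end of study. Section 2.3 gives two of these values an analysis role: "As explorative endpoints, we will also consider changes (per month) in" a list that includes vitamin D and creatinine. The monthly change in creatinine is also a covariate in a supportive model for gait speed (section 8.2).

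**The concern.** The Protocol screens patients at entry on kidney function, calcium metabolism and vitamin D and calcium intake. It then takes blood that bears on most of these at both visits. Nothing says that the results will be looked at as safety.

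An asymptomatic rise in creatinine is not gastrointestinal and may not be serious, so under section 6.3 it is no safety event. The same holds for a newly abnormal urea nitrogen, electrolyte or 25(OH)D value. Safety is a declared secondary endpoint, and section 6.3 opens by calling the product safe on the strength of earlier trials. The trial could repeat that conclusion without having counted any patient whose renal, electrolyte or vitamin D value became abnormal.

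A related gap concerns supplements started later. The Introduction counts vitamin D supplementation as part of basic sarcopenia treatment, so it could plausibly be started during the stay, but the Protocol has no record of this.

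**Working it through.** The Protocol gives no figure on this point to reproduce. The check is a comparison of sections.

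**Step 1. Which events does section 6.3 collect?**

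| Event type | Gastrointestinal | Renal, calcium or other |
|---|---|---|
| Non-serious | monitored | not named |
| Serious, expected | monitored | not named |
| Serious, unexpected | recorded | recorded |

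Two cells are empty: non-gastrointestinal events that are non-serious, and those that are serious but expected.

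**Step 2. Does another section fill those cells?** Section 2.2 names safety without content. In the schedule, the safety row is separate from the biochemistry row and is marked only at end of study, while biochemistry is marked at both visits. The layout therefore gives no sign that laboratory values belong to safety. Section 8.2 defines who is in the safety population, not what is measured. Nothing widens section 6.3.

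**Step 3. What becomes of the blood values?**

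| Value | Taken at both visits | Analysis role | Safety outcome |
|---|---|---|---|
| Creatinine | yes | exploratory change per month; covariate in a supportive model | no |
| Urea nitrogen | yes | none | no |
| Serum electrolytes | yes; calcium not named | none | no |
| 25(OH)D | yes | exploratory change per month | no |

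None of the four is a safety outcome, and two of the four belong to no endpoint. It is not certain that calcium is measured, because it is taken only if the electrolyte panel includes it.

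**Step 4. Does change per month serve as a safety measure?** It answers a different question. Observation lasts 4 to 8 weeks. The same absolute rise x gives x/4 per week for a patient seen at 4 weeks and x/8 for one seen at 8 weeks, and (x/4)/(x/8) = 2. Two patients with the same abnormal final value and the same rise can therefore differ twofold on this scale. The scale also does not show whether a patient crossed a reference limit.

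**Step 5. Are later supplements captured?** Section 6.1 collects medications under medical history, apparently as a number, and the schedule places this at baseline only. The dietary assessment estimates energy and macronutrients. The diary counts servings of the study formula. None would show a vitamin D or calcium product started after randomisation.

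**Step 6. Who would have a second sample?** The safety population needs only one serving, but the second blood sample is at end of study. At the planned 10% dropout, 0.10 × 140 = 14 randomised patients may have no second sample. Any count of new abnormalities needs its own denominator.

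**The case against.** The case on the other side has real force on several points.

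- **The link to the exclusions can be overread.** A reader might infer that section 4.2 labels kidney function and calcium metabolism as risks of the product. It does not. Only the vitamin D, calcium and diet or protein-supplement items stand in the product-related sub-list; kidney failure and calcium disorders are separate entries beside malignancy and liver failure. The intake limits concern medical sources, not total intake, and the sub-list may serve to avoid confounding as much as to protect patients.
- **The amounts in the formula do not show harm.** Two servings supply 2 × 800 = 1600 IU of vitamin D and 2 × 500 = 1000 mg of calcium a day. A reader might set these against the 400 IU and 500 mg entry limits and infer a hazard. Those limits apply to other medical sources, and the documents give no ceiling against which to judge the product.
- **An outlier need not be hidden.** Section 8.2 plans range, median and quartiles as well as the mean, so a large individual rise in creatinine or vitamin D may be visible. It would be wrong to say that it must be averaged away.
- **Glucose does not belong here.** It is measured and has no endpoint, and a reader might extend the point to the maltodextrin control, but no exclusion criterion refers to it.
- **Table layouts are commonly left to the SAP**, which is not shown.

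The first four points narrow the concern without removing it. The fifth holds for the form of a table but not for the scope of safety collection, which section 6.3 itself fixes. A range also does not count patients with new abnormalities, and section 2.3 gives urea nitrogen and electrolytes no analysis at all.

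**Conclusion.** The point holds in limited form and should be corrected. As written, no laboratory value is a safety outcome. Non-gastrointestinal events that are non-serious, or serious but expected, fall outside the safety collection. No count of newly abnormal renal, electrolyte or vitamin D values is planned, and supplements started after randomisation go unrecorded.

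The documents do not support saying that these values are ignored, that serious renal or calcium events would be missed altogether, or that the product is unsafe. Creatinine and vitamin D are pre-specified exploratory endpoints, and unexpected serious events are recorded whatever the organ system.

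The effect is on what the secondary safety endpoint can conclude. The primary endpoint, its power and the sample size do not change. The conclusion assumes that section 6.3 is the full statement of safety collection, which the rest of the Protocol bears out, and that medications are collected at baseline only, as the schedule shows.

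**What to change.** 1. In section 6.3, name creatinine, urea nitrogen, serum electrolytes and 25(OH)D as safety outcomes, and state whether calcium is among the electrolytes.
2. Report by arm, among safety-population patients with both samples, how many moved from inside to outside the laboratory's reference limits. State how many patients in each arm lack a second sample.
3. Report the largest individual changes by arm in original units, not divided by months.
4. Record any vitamin D or calcium product started after randomisation, and report it by arm.

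This needs a few lines of text, one extra table, one medication field, and a calcium measurement on the same tube if the electrolyte panel lacks it. No visit is added, and the interventions, sample size and primary analysis stay as they are. The limitation is that patients who leave early may still have no second sample; item 2 shows their number but does not recover their data.

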# **Statistics and sample size**

***8.1 Sample size***

In the absence of preliminary data to estimate the expected treatment difference, the sample size was set at 128 patients reaching the evaluation of the primary endpoint (64 per arm) to achieve a statistical power of 80% (type I error 5% using a two-tailed test) to detect a clinically meaningful difference (mean treatment difference/standard deviation [effect size]=0.5). Allowing for a 10% drop-out rate in each arm, it was decided to randomize 140 patients (70 per treatment arm).

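### Recording of serious adverse events is limited to undefined unexpected ones, so total serious events cannot be reliably compared between arms

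*Protocol*

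**What the plan says.** Section 2.2 of the protocol lists "safety of the intervention" among the secondary endpoints. Section 8.2 defines the population for it: "All patients consuming at least one serving of nutritional formula will be included in the safety analysis".

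The rule for what is collected stands in section 6.3 and has two parts. The first covers effects of the product: "Patients will be actively monitored for the occurrence of any potential gastrointestinal side effect associated with the consumption of the nutritional intervention formula", which the section labels as common adverse events. The second covers serious events: "The occurrence of any unexpected serious adverse event will also be recorded". Neither this section nor any other says what makes a serious event unexpected.

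Section 8.2 ends with a separate list, introduced by "The following causes of dropout will be considered". It names death, loss to follow-up through hospitalization or transfer to another care setting, and withdrawal. Nothing there links the list to the safety analysis.

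**The concern.** Expectedness is ordinarily used after an event has been recorded, to decide how it is reported. Here it is applied earlier and decides whether a serious event is recorded at all. Participants are in-patients aged 65 or over with sarcopenia, and the rehabilitation profiles in section 6.1 include patients with important concomitant diseases. Many serious events in such patients are foreseeable on clinical grounds, so an assessor could reasonably call them expected and leave them out.

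Randomization makes background events comparable between arms, but only if they are all counted. A statistical analysis plan may exist for this trial, but it could not repair this point, because no analysis recovers events that were never written down. What is at stake is whether a safety statement from this trial can rest on a full count of serious events in each arm.

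**Working it through.** The protocol gives no figure on this point, so the check compares sections 2.2, 2.3, 6, 6.1, 6.3 and 8.2 and asks where each kind of event would be captured.

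**Step 1: the two possible meanings.** Since the term is undefined, two readings are open.
- *Product-based:* expected means the known gastrointestinal effects of the formula. Anything else serious is unexpected and is recorded.
- *Population-based:* expected means foreseeable in older, sarcopenic rehabilitation patients. A foreseeable serious event need not be recorded.

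**Step 2: capture under each reading.**

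| Event | Product-based | Population-based |
|---|---|---|
| Gastrointestinal side effect of the formula, any severity | Captured by active monitoring | Captured by active monitoring |
| Death | Captured as a serious event and as a drop-out cause | Captured as a drop-out cause; entry into the safety analysis not stated |
| Hospitalization or transfer ending participation | Captured as a drop-out cause; the serious event behind it also recorded | Captured as a drop-out cause; the event behind it need not be recorded |
| Hospitalization not ending participation | Recorded | Need not be recorded if foreseeable |
| Fall with fracture, or infection treated on the unit, patient stays | Recorded | Need not be recorded |

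The readings agree on the first row. They differ on the last two rows, and on whether deaths and transfers count as safety events or only as disposition.

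**Step 3: effect on the comparison.** Section 8.2 says a treatment effect with a 95% confidence interval will be reported for all endpoints, as a frequency difference where the outcome is binary. Let p1 and p0 be the true proportions of patients with a serious event in the experimental and control arms, and let r be the share of those patients whose event passes the filter.
- If r is the same in both arms, the recorded difference is r·p1 − r·p0 = r·(p1 − p0). It shrinks toward zero as r falls, and both recorded rates are too low by the factor r.
- If the product alters the mix of event types, r differs by arm (r1 and r0), and r1·p1 − r0·p0 need not even have the sign of p1 − p0.

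On the product-based reading r is close to 1. On the population-based reading it is below 1 by an amount the protocol gives no means of estimating. I therefore put no number on r, p1 or p0.

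**The case against.** The strongest defence is the product-based reading. Section 6.3 speaks about the product throughout: earlier trials of this food, then the gastrointestinal effects of the formula, then unexpected serious events. In that context a fracture or an infection is unexpected and would be recorded, and little would be lost. This reading is plausible and limits how far the point can be pressed. It is not stated, however, and the sentence allows the other reading equally. The trial is also double-blind, which makes it less likely that the judgement favours one arm. Blinding does not restore missing events, and it does not keep r equal if the mix of events differs by arm.

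A reader might infer more than the protocol supports:

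- *That the arms cannot be compared on deaths and hospital transfers.* Those that end participation are named as drop-out causes in section 8.2 and can be tabulated by arm. The gap is that they are not placed in the safety analysis.
- *That serious gastrointestinal events are lost.* Section 6.3 covers any such side effect, without a severity limit.
- *That a decline in kidney function would go unseen.* Creatinine is measured at baseline and at the end of the study, and its change is an exploratory endpoint in section 2.3.
- *That the assessment table in section 6 restricts safety collection to the final visit.* Compliance is marked in the same way there, although section 5.2 has it recorded daily in a diary.
- *That most serious events would be omitted, or a particular number of them.* The protocol gives no serious-event rate, and the share lost depends on an undefined word.

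**Conclusion.** The point holds in limited form. Section 6.3 filters serious adverse events at the moment of recording by an undefined criterion. Foreseeable serious events in patients who remain in the study need not be recorded, and deaths and transfers sit outside the stated safety analysis. The secondary safety endpoint therefore cannot give a reliable comparison of total serious adverse events between arms.

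The loss is possible, not certain, and its extent is unknown. It is close to nil if site staff adopt the product-based reading and could be material if they adopt the population-based one. Confidence is moderate, because the conclusion rests on the second reading being genuinely open. The primary endpoint and the sample size are not affected. The change should be made because it is cheap and because unrecorded events cannot be recovered later.

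**What to change.** Replace the sentence on serious events in section 6.3 with the following:

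*All serious adverse events, whether or not expected or related, will be recorded from the first serving until discharge or drop-out and tabulated by arm in the safety population, including deaths and hospitalizations or transfers listed as drop-out causes; expectedness and relatedness will be classified afterwards.*

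This removes the need to settle the meaning of unexpected before an event is entered. It also joins the drop-out list in section 8.2 to the safety analysis.

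The cost is a wording change and slightly more recording work for 140 in-patients at one site. The safety table will look less favourable, because background events in both arms will appear in it. No treatment, efficacy endpoint or sample size changes.
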